### Who will take informed consent? {26a}

Each participant must provide written consent according to local requirements after the nature of the study has been fully explained to them. Written informed consent is provided by signing the informed consent form (ICF) before participation in any study-related activity. The ICF must be approved by both the sponsor/designee and by the reviewing IEC/IRB and written in a language that the participant can read and understand. Informed consent should adhere to principles as outlined in the Declaration of Helsinki, current ICH and GCP guidelines, applicable regulatory requirements, and sponsor/designee policies.

Before a potential participant is enrolled in the study, the investigator or an authorized study-site staff member must explain to him/her the aims, methods, reasonably anticipated benefits and potential hazards of the study, and any discomfort associated with study participation. Participants will be informed that their participation is voluntary, that they may withdraw consent to participate in the study at any time, and that choosing not to participate will not affect their care. Finally, participants will be informed that the investigator will maintain a participant identification register for use in providing long-term follow-up care (as needed) and that their records may be accessed by health authorities and authorized sponsor/designee personnel without violating participant confidentiality to the extent permitted by applicable laws or regulations. By signing the ICF, the participant is authorizing such access.

The participant will be given sufficient time to read the ICF and then will be provided an opportunity to ask questions. Thereafter, consent should be appropriately recorded as the participant’s personally dated signature on the ICF prior to study participation. After participant consent is obtained, a copy of the signed ICF must be given to the participant. A participant who is rescreened for study suitability is not required to sign another ICF if rescreening occurs within 30 days from the previous ICF signature date.

If the participant is unable to read or write, an impartial witness should be present during the entire informed consent process (which includes reading and explaining all written information) and should personally date and sign the ICF after the participant oral consent is obtained.

### Additional consent provisions for collection and use of participant data and biological specimens {26b}

Separate consent forms are needed for ancillary studies.

### Interventions

PROSPECT is a registration-related study to provide evidence of BDQ-containing SCR in Chinese based on STREAM. The experimental arm is modified based on STREAM regimen C (an oral regimen consisting of BDQ, LFX, CFZ, EMB, and PZA administered for 40 weeks, supplemented by high-dose INH and PTO in the first 16 weeks) and the control arm is modified according to STREAM regimen B (an injectable-containing regimen consisting of MFX or LFX, CFZ, EMB, and PZA administered for 40 weeks, supplemented by KM or AM, high-dose INH, and PTO in the first 16 weeks).

#### Explanation for the choice of comparators {6b}

The SCR without BDQ consists of LFX (40 weeks), LZD (at least 24 weeks), CS (40 weeks), CFZ (40 weeks), pyrazinamide (PZA) (40 weeks), and PTO (initial 16 weeks) and is designed to serve as a comparator under self-administration trained by appointed nurses The control arm treatment is modified by removing high-dose INH and injectable KM, then regimen efficacy is enhanced by adding LZD and CS based on Regimen B of STREAM trial.

#### Intervention descriptions {11a}

Experimental arm participants will be instructed to self-administer the assigned dose of BDQ in combination with the following four drugs: LFX (40 weeks), LZD (at least 24 weeks), CS (40 weeks), and CFZ (40 weeks). During the study treatment phase, these participants will receive an all-oral SCR consisting of 24 weeks of BDQ in combination with 40 weeks of other allocated TB treatment drugs (except for LZD, which will be administered for at least 24 weeks). If a participant is still sputum culture-positive for *MTB* by week 16, BDQ treatment will be extended from 24 to 40 weeks.

Detailed information for drugs administered to trial participants is provided in Table 2.

**Table 2 Tab2:** Detailed information for the individual drug of each arm in the PROSPECT study

Drug	BDQ	LFX	LZD	CS	CFZ	PZA	PTO
BDQ-containing regimen (duration [weeks])	X (24 to 40)^a^	X (40)	X (≥ 24)	X (40)	X (40)		
Non-BDQ-containing regimen (duration [weeks])	NA	X (40)	X (≥ 24)	X (40)	X (40)	X (40)	X (First 16)
Dosage formulation	Uncoated tablet	Film-coated tablet	Tablet	Capsule	Capsule	Tablet	Enteric-coated tablet
Unit dose strength	100 mg	100 mg and 500 mg	600 mg	250 mg	50 mg	250 mg	100 mg
Dose regimen	400 mg once daily for the first 2 weeks, 200 mg 3 times per week (with at least 48 h between doses) for the remaining weeks (i.e., 22 weeks or 38 weeks in case bedaquiline treatment is extended to 40 weeks)	30–35 kg: 600 mg daily 36–55 kg: 750 mg daily > 55 kg: 1000 mg daily	600 mg daily	30–45 kg: 500 mg daily > 45 kg: 750 mg daily	100 mg daily	30–35 kg: 1000 mg daily 36–70 kg: 1500 mg daily > 70 kg: 2000 mg daily	30–45 kg: 500 mg daily 46–70 kg: 600 mg daily > 70 kg: 800 mg daily

^a^If a participant is still sputum culture-positive for *MTB* by week 16, BDQ treatment will be extended from 24 to 40 weeks

*NA*, not available

#### Criteria for discontinuing or modifying allocated interventions {11b}

A participant’s study intervention must be discontinued if:The participant withdraws consent to receive the study intervention.The investigator believes that for safety or tolerability reasons it is in the best interest of the participant to discontinue the study intervention. Individual drug substitutions within the study intervention regimen may be considered if clinically indicated at the discretion of the investigator. Administration of single-drug substitutions will not be viewed as an unfavorable treatment outcome criterion if limited to substitutions of non-group A drugs (except DLM) as per the 2020 WHO MDR-TB treatment guidelines.The participant becomes pregnant.Unacceptable toxicity.The patient experiences:Aminotransferase elevations with total bilirubin elevations to levels of ≥ twofold the ULNAminotransferase elevations to levels that are ≥ eightfold greater than the ULNAminotransferase elevations to levels that are ≥ fivefold greater than the ULN and persist for more than 2 weeks.If the patient experiences a QTcF interval > 500 ms (as confirmed by repeat ECG) and/or clinically significant ventricular arrhythmia.Noncompliance with study drug administration.Any participant not meeting eligibility criteria as specified in the “Eligibility criteria” section.

A participant will be withdrawn from the study for any of the following reasons:If phenotypic DST results from a screening sample become available post-baseline confirming resistance at the start of the study to any of the drugs in the assigned regimen except BDQ, in which case the patient will be treated according to local treatment protocols after withdrawal from the study.Lost to follow-up.Withdrawal of consent.Death.

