**Methods:**

This phase 4, randomized, open-label, controlled, non-inferiority trial aims to assess the efficacy and safety of a 9-month all-oral SCR containing bedaquiline (BDQ) *versus* an all-oral SCR without BDQ for adult MDR-TB patients (18–65 years) in China. The trial design mainly mirrors that of the “Evaluation of a Standardized Treatment Regimen of Anti-Tuberculosis Drugs for Patients with MDR-TB” (STREAM) stage 2 study, while also incorporating programmatic data from South Africa and the 2019 consensus recommendations of Chinese MDR/RR-TB treatment experts. Experimental arm participants will receive a modified STREAM regimen C that replaces three group C drugs, ethambutol (EMB), pyrazinamide (PZA), and prothionamide (PTO), with two group B drugs, linezolid (LZD) and cycloserine (CS), while omitting high-dose isoniazid (INH) for confirmed INH-resistant cases. BDQ duration will be extended from 6 to 9 months for participants with *Mycobacterium tuberculosis*-positive sputum cultures at week 16. The control arm will receive a modified STREAM regimen B without high-dose INH and injectable kanamycin (KM) that incorporates experimental arm LZD and CS dosages, treatment durations, and administration methods. LZD (600 mg) will be given daily for ≥ 24 weeks as guided by observed benefits and harm. The *primary outcome* measures the proportion of participants with favorable treatment outcomes at treatment completion (week 40), while the same measurement taken at 48 weeks post-treatment completion is the *secondary outcome*. Assuming an *α* = 0.025 significance level (one-sided test), 80% power, 15% non-inferiority margin, and 10% lost to follow-up rate, each arm requires 106 participants (212 total) to demonstrate non-inferiority.

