In 2019, the WHO published consolidated drug-resistant TB (DR-TB) treatment guidelines that included key changes made to MDR/RR-TB treatment protocols [11]. The revised guidance introduces a priority ranking-based classification scheme for available anti-TB treatment drugs. In this scheme, BDQ is recommended and prioritized for use as a core drug (Group A) in the longer-course MDR/RR-TB treatment regimen, with LZD also recommended for inclusion as a core drug. A third Group A drug, such as levofloxacin (LFX) or moxifloxacin (MFX), and at least one Group B drug, such as clofazimine (CFZ), cycloserine (CS), or terizidone (TZD), are recommended for use in the longer-course MDR/RR-TB treatment regimen to ensure that at least four potentially effective TB agents are administered at treatment initiation. As an additional modification, kanamycin (KM) and capreomycin (CM) were deprioritized as components of MDR/RR-TB treatment regimens [11]. Meanwhile, the “Chinese expert consensus of MDR-TB and RR-TB treatment” guidelines issued in October 2019 recommend the reprioritization of certain drugs, as based on WHO 2019 guidance recommending the incorporation of BDQ in both long-course regimens (LCRs) and SCRs used to treat MDR-TB patients [12].

In December 2019, the WHO issued a Rapid Communication [13] advocating the adoption of a shorter-course, all-oral, BDQ-containing regimen for MDR/RR-TB patients to replace the standard shorter-course injectables-based regimen. At the same time, the results of a study conducted in South Africa [14, 15] prompted the WHO to recommend transitioning away from the standard regimen. These revisions are incorporated within the current WHO consolidated guidelines issued in 2020 [16] along with guidelines for administering a shorter-course (9–12-month) all-oral BDQ-containing regimen for treatment of eligible MDR/RR-TB cases lacking both resistance to fluoroquinolones (FQs) and prior treatment histories of greater than 1-month’s duration to second-line TB drugs included in the shorter-course, all-oral regimen.

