As access to newer and repurposed TB drugs increases, Chinese researchers are increasingly focused on developing shortened regimens with lower toxicity and non-inferior or better efficacy that eliminate the need for injectables. The “Pragmatic Randomized Controlled Trial to Evaluate the Efficacy and Safety of an Oral Short-course Regimen Including BDQ for the Treatment of Patients with Multidrug-resistant Tuberculosis in China” (PROSPECT) was designed to compare the safety and efficacy of a modified 40-week all-oral, BDQ-containing SCR MDR-TB treatment to corresponding performance indicators of a 40-week all-oral SCR without BDQ. The design of the new MDR-TB treatment regimen, which primarily incorporates key drugs of regimens B and C evaluated in the STREAM stage 2 study [6], was further modified based on recommendations of experts, as indicated in the 2019 “Chinese expert consensus of MDR-TB and RR-TB treatment” guidelines^12]^. For the experimental arm treatment, modifications were made to the original STREAM regimen C. In accordance with principles governing LCR design, the three group C drugs EMB, PZA, and PTO were replaced with the two group B drugs LZD and CS and high-dose INH, while BDQ treatment duration was increased from 6 to 9 months for participants who were still sputum culture-positive for *MTB* at week 16. For the control arm, an 18–20-month injectables-based regimen, the recommended standard of care (SOC) MDR-TB treatment since 2016 [17], was replaced with the WHO-endorsed shorter-course 9–11-month injectables-based regimen in 2018 [18]. However, modified standardized shorter-course MDR-TB regimens are currently being developed for Chinese MDR-TB patients. For example, the PROSPECT control arm receives a modified treatment, whereby KM is replaced with LZD to remove the need for injectables that are no longer recommended by the WHO. Additionally, high-dose INH was removed, due to concerns stemming from (1) the high *KatG* mutation rate observed in INH-resistant *MTB* isolates obtained from patients in China, which implies that most Chinese TB cases with high-level INH resistance will not benefit from high-dose INH; (2) the small proportion of Chinese MDR-TB patients who carry a certain *ihnA* mutation who may benefit from high-dose INH treatment should be excluded, due to PTO cross-resistance conferred by this mutation; and (3) the safety profile of high-dose INH when used to treat Chinese patients has not been verified. In summary, the PROSPECT experimental arm modifications were made based on the original STREAM regimen C and the control arm regimen was modified based on the regimen B used in the STREAM study [6], by removing high-dose INH and injectable KM and intensified by incorporating LZD and CS.

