### Outcomes {12}

#### Primary outcomes

The primary outcome is the proportion of participants with a favorable treatment outcome at treatment completion (week 40). In this work, patient outcomes will be classified as favorable if their last three culture results prior to treatment completion are negative, unless they had previously been classified as unfavorable. These three cultures must be taken on separate visits, the latest of which will be taken no more than 8 weeks prior to the treatment completion date. Unfavorable outcomes include the following: treatment discontinuation; starting 2 or more drugs not in the allocated regimen; treatment continuation beyond the permitted duration; death; lost to follow-up prior to treatment completion; relapse and re-infection. Treatment success is achieved if participants completed their prescribed TB treatment or if their last three culture results by the end of treatment are negative (these 3 cultures must be taken on separate visits).

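### The discontinuation section and the primary outcome definition give two different rules for whether a single-drug substitution makes a patient unfavourable

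*Protocol article*

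**What the plan says.** Protocol article, Criteria for discontinuing or modifying allocated interventions {11b}: individual drugs may be substituted at the investigator's discretion, and "Administration of single-drug substitutions will not be viewed as an unfavorable treatment outcome criterion if limited to substitutions of non-group A drugs", with an exception for DLM and the grouping taken "as per the 2020 WHO MDR-TB treatment guidelines".

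Protocol article, Outcomes {12}, Primary outcomes: a patient is favourable at week 40 if the last three cultures are negative, unless already classified as unfavourable. The list of unfavourable events begins "Unfavorable outcomes include the following: treatment discontinuation" and has one criterion on new drugs, "starting 2 or more drugs not in the allocated regimen". It sets no Group A or DLM condition and does not refer back to {11b}.

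On linezolid, the Abstract (Methods) says that three drugs are replaced "with two group B drugs, linezolid (LZD) and cycloserine (CS"). The design rationale in Background {6a} repeats the label: "replaced with the two group B drugs LZD and CS and high-dose INH". Earlier in the same Background section, the account of the 2019 WHO guidance equates core drug with Group A for bedaquiline, continues "with LZD also recommended for inclusion as a core drug", and then calls the fluoroquinolone the third Group A drug. That makes linezolid the second. Table 2 puts linezolid in both arms.

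**The concern.** The clause in {11b} is written in endpoint language: it says when a substitution does not count against the patient. Its condition has a purpose only if some single substitutions do count. The outcome definition contains no such case, because one new drug never reaches its threshold of two. The two sections can therefore classify the same patient differently on the primary endpoint.

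The trial is open-label {17a}, and the investigator who decides on a substitution knows the arm. If the rule is settled only when outcomes are being classified, the choice can change the event count in each arm, and so the estimated difference that is compared with the 15-point margin. The linezolid label adds a practical risk: anyone who classifies from the protocol's own labels may put linezolid in the wrong group.

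**Working it through.** **Side by side.** Take a patient with one substitution, three negative cultures and no other unfavourable event.

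| Single substitution | {11b} | Outcome definition {12} |
|---|---|---|
| Non-Group A drug, not DLM | not unfavourable | favourable (one new drug) |
| Group A drug or DLM | unfavourable, by implication | favourable (one new drug) |

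The sections agree in the first row and differ in the second.

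**Removed or added?** Section {11b} does not say which drug must be non-Group A. DLM is in neither regimen (Table 2), so excepting it makes sense mainly if the drug added is meant. The conflict with {12} survives both readings:
- Drug removed: one replacement for bedaquiline, levofloxacin or linezolid falls in the second row.
- Drug added: a control patient who starts bedaquiline as the only new drug falls in the second row. Linezolid and levofloxacin are already in both arms, so the linezolid label matters little here.

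**The plan's own figure.** Inputs from Sample size {14}: 85% control rate, margin 0.15, one-sided alpha 0.025, power 80%, 95 evaluable per arm, 10% not evaluable. Equal 85% rates under the alternative are assumed. Farrington-Manning sample size per arm:

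n = [(1.960·s0 + 0.842·s1) / 0.15]²

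- Rates restricted to a 15-point difference: 0.8989 and 0.7489, so s0 = √(0.8989·0.1011 + 0.7489·0.2511) = 0.528.
- s1 = √(2·0.85·0.15) = 0.505.
- n = 94.8, so 95 per arm. Then 95/0.90 = 105.6, so 106 per arm and 212 in total. The stated size reproduces and is not in dispute.

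**Illustration.** The documents give no substitution rate. Assume that 85% per arm are favourable under {12} and that a share r of them becomes unfavourable under {11b}. The rate is then 0.85·(1 − r). With D = BDQ rate minus control rate:

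power = Φ{[(0.15 + D)·√95 − 1.960·s0] / s1}

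with s0 and s1 recomputed for each pair of rates.

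| r, BDQ arm | r, control | BDQ rate | Control rate | D (points) | Power |
|---|---|---|---|---|---|
| 0% | 0% | 85.0% | 85.0% | 0 | 80% |
| 2% | 2% | 83.3% | 83.3% | 0 | 77% |
| 3% | 2% | 82.45% | 83.3% | −0.85 | 72% |
| 5% | 5% | 80.75% | 80.75% | 0 | 73% |
| 10% | 10% | 76.5% | 76.5% | 0 | 68% |
| 15% | 10% | 72.25% | 76.5% | −4.25 | 40% |
| 5% | 10% | 80.75% | 76.5% | +4.25 | 89% |

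A 5-percentage-point imbalance moves D by 0.85·0.05 = 0.0425, and 4.25/15 = 28% of the margin.

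**The case against.** **The conflict is only implied.** Section {11b} never states that a Group A substitution is unfavourable. The list in {12} is introduced as inclusive, and treatment discontinuation is not limited to the whole regimen, so {11b} might be read as a supplement. It is true that the conflict is by implication. But if discontinuation covered stopping one drug to replace it, every single-drug swap would be unfavourable, which contradicts {11b} for non-Group A drugs. If {11b} supplements {12}, the outcome definition still omits a criterion that decides the primary endpoint.

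**The linezolid label does not set the rule.** This stands. Section {11b} takes its grouping from the 2020 WHO guidelines, not from the Abstract or the design rationale. A reader might infer that the Group B label itself makes the endpoint ambiguous. The text supports only a labelling error that invites misclassification.

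**A fixed asymmetry against bedaquiline.** A reader might infer one because, by the Background grouping, the BDQ arm has three Group A drugs and control two. That holds only if the drug removed is meant. If the drug added is meant, control could add bedaquiline or moxifloxacin. The BDQ arm has almost no Group A drug named in the Background left to add, since moxifloxacin is prohibited until 30 days after the last bedaquiline dose. The direction could then reverse. Nor is the count rule in {12} shown to be neutral, as control has six drugs and the BDQ arm five.

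**The size is assumed.** This also stands. A reader might call the shift comparable with the margin, but the 4.25 points in the illustration are under a third of it, and lower rates give less.

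**The statistician is blinded.** The Discussion says so, and the full protocol and analysis plan may settle the rule. Later choice of a rule is therefore a risk and not an expectation. The blinding does not extend to the investigators who decide on substitutions.

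**Conclusion.** The point holds as a drafting conflict on the primary endpoint: the article states two rules for a single-drug substitution, and they disagree for a Group A drug or DLM. Section {11b} also leaves open whether removal or addition counts. The linezolid label is a separate error with a smaller consequence.

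The effect on the result cannot be derived from the documents. Under the assumed rates (95 per arm, 85% favourable before reclassification), equal reclassification of 2% to 10% costs about 3 to 12 points of power. An imbalance of 5 percentage points moves the difference by about 4.25 points, with power between 40% and 89% according to direction. No direction is established, and the planned sample size is unaffected.

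**What to change.** - Put one substitution rule in the outcome definition {12}, applied identically in both arms. Name the drugs and state whether the drug removed or the drug added counts.
- Align the outcome clause in {11b} with it, or replace the clause by a cross-reference.
- Correct the linezolid group label in the Abstract and in the design rationale in Background {6a}.
- Prespecify the other reading as a sensitivity analysis of the primary endpoint.
- Do this before outcomes are classified.

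The choice of rule is the sponsor's. The change concerns endpoint classification only and leaves the clinically permitted substitutions as they are. The cost is protocol and analysis-plan wording and one extra analysis, with no change to sample size or visits.

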#### Strategies to improve adherence to interventions {11c}

BDQ and other allocated TB treatment drugs will be administered orally after screening either in a hospital or home setting according to site protocols. When participants are dosed in the hospital, the date of each dose will be recorded in the source documents and case report forms (CRFs) by designated study-site personnel. The study intervention dose, allocated TB treatment drugs, and study participant identifier will be confirmed at the time of dosing by a study-site staff member other than the person administering the study intervention.

For participants who self-administer the study intervention at home, patient compliance with the study intervention protocol will be assessed at each visit by counting remaining tablets/capsules during site visits and documenting this information in source documents and CRFs. Deviations from the prescribed dosage regimen should be recorded in the CRFs. A record of the number of tablets/capsules dispensed to and consumed by each participant must be maintained and reconciled with study intervention and compliance records. Intervention start and stop dates, including dates for intervention delays and/or dose reductions, will also be recorded in CRFs.

